### Eligibility Criteria

The key inclusion criteria are as follows: (1) metastatic solid tumours not for curative intent therapy; (2) planned for treatment with the following chemotherapy regimens: XELOX, XELIRI or single-agent capecitabine; (3) presence of raised tumour marker above upper limit of local laboratory normal (e.g., CEA, CA19-9); (4) males and females ≥21 years of age (the age of majority in Singapore); (5) Eastern Cooperative Oncology Group (ECOG) Performance Status of 0 to 2; (6) meet the following clinical laboratory criteria within 21 days of starting treatment: (a) Absolute neutrophil count (ANC) ≥1,000/mm3 and platelet ≥50,000/mm3, (b) total bilirubin ≤ 1.5x the upper limit of the normal range (ULN) and alanine aminotransferase (ALT) and aspartate aminotransferase (AST) ≤ 3x ULN or ≤ 5x ULN in the of the liver involvement, (c) calculated creatinine clearance ≥30 mL/min or creatinine <1.5x ULN.

The key exclusion criteria as follows: (1) currently lactating or pregnant; (2) major surgery within 28 days prior to start of the treatment; (3) active congestive heart failure (New York Heart Association [NYHA] Class III or IV), symptomatic ischaemia, conduction abnormalities uncontrolled by conventional intervention or myocardial infarction within 4 months prior to date of obtaining informed consent; (4) clinically significant hypersensitivity to one or more of the selected regimen's constituent drug(s); (5) contraindication to any of the required concomitant drugs or supportive treatments; (6) any clinically significant medical disease or psychiatric condition that, in the investigator's opinion, may interfere with protocol adherence or a participant's ability to give informed consent.

### Interventions

#### Definition of CURATE.AI

CURATE.AI in this context refers to the CURATE.AI platform (software), engineering expertise in operating the CURATE.AI platform, drug dose recommendations generated by the CURATE.AI platform and accompanying analyses of clinical data. The Health Sciences Authority in Singapore classifies CURATE.AI as a Class B medical device (low to moderate risk), which is defined as all active therapeutic devices that are software, or which are intended to administer or exchange energy to or with the human body. We have filed the accompanying Clinical Research Materials notification under the National University of Singapore, for the intended purpose of providing dose recommendations within this pilot clinical trial. The CURATE.AI internal workflow is summarised in Figure 1 and explained in subsequent sections.

**Figure 1 F1:**
[figure not shown]
Internal workflow for optimising combination therapy modulation with CURATE.AI for solid tumours, including scenarios that may lead to recalibration.

#### CURATE.AI Built-In Safety Mechanisms

All doses recommended by CURATE.AI will always be within the safe dose range pre-specified by the clinical investigator: (1) the predetermined safety range (50–100% of dose used in standard-of-care treatment) and (2) participant-specific dosing range (accounting for the specific participant's personal medical history and clinical context). If CURATE.AI is unable to recommend a dose that fulfils the above requirements, it will not recommend a modulated dose and the clinical investigator will decide the dose according to the standard-of-care. Should the participant experience clinically relevant grade 3 or 4 non-haematological toxicity at a particular dose, we will restrict the next dose recommendation by CURATE.AI to a lower dose. Clinical investigators will have the final say on whether to use the CURATE.AI-recommended dose. Clinical investigators may also adjust the dose beyond CURATE.AI's recommendations as they deem necessary.

#### CURATE.AI Calibration-Intent Dose Recommendations

For every participant, CURATE.AI will undergo an initial calibration stage (Figure 1, Steps 1–4) with the aim of generating a personalised CURATE.AI profile based on that participant data only. CURATE.AI will provide calibration-intent dose recommendations (Figure 1, Step 1) to collect data on the participant's phenotypic response (measured by tumour markers e.g., CEA, CA19-9) to a range of drug doses (Figure 1, Step 2). Any dose recommended by CURATE.AI to the clinical investigator will always be within the pre-specified safe dose range.

CURATE.AI requires a minimum of three unique data pairs (capecitabine dose and tumour marker), with one data pair collected per cycle, to generate the personalised CURATE.AI profile (Figure 1, Step 3) based on a second-order polynomial. After giving participants capecitabine at calibration-intent doses and measuring the corresponding tumour marker levels, we will analyse the data to determine if they fulfil calibration requirements. If not, CURATE.AI will make further calibration-intent dose recommendations and more data pairs will be collected until the CURATE.AI profile can be generated.

#### CURATE.AI Efficacy-Driven Dose Recommendations

After the CURATE.AI profile is generated, we will check it for actionability, defined as the ability to recommend an optimum dose within the safety requirements pre-specified by the clinical investigator (Figure 1, Step 4). For participants with actionable profiles, CURATE.AI will recommend therapeutic-intent, efficacy-driven doses to the clinical investigator (Figure 1, Step 5). Any dose recommended by CURATE.AI will always be within the safe dose range pre-specified by the clinical investigator. If the dose-dependent relationship is maintained, CURATE.AI will continue to use the existing profile to provide dynamic dose recommendations before every subsequent cycle (Figure 1, Step 6.1). This continues until the end of the participant's involvement in the study (Figure 1, Step 7), which is when the clinical investigator decides to cease/change the chemotherapy regimen, or until 12 months, whichever is earlier. If the dose-dependent relationship is not maintained but we do not suspect systemic changes in the participant (Figure 1, Step 6.2), CURATE.AI will obtain a new data pair in the next cycle based on the existing profile. If the dose-dependent relationship is not maintained and we suspect systemic changes in the participant at any point during the trial, such as but not limited to the introduction of haemodialysis or drugs with known interactions with the treatment, CURATE.AI may recalibrate the personalised profile (Figure 1, Step 6.3) to generate a new profile for the participant. CURATE.AI will select recalibration doses on the basis of previous correlations.

### Objectives

#### Primary Objective

Our primary objective is to assess the technical and logistical feasibility of an RCT for CURATE.AI-guided dosing with the selected chemotherapy regimens and tumour markers. Technical feasibility is defined by the following questions: (1) whether CURATE.AI profiles can be successfully created and applied; (2) whether the specific patient characteristics that predict the successful creation and applicable of CURATE.AI profiles can be identified; (3) whether the CURATE.AI-recommended dose is substantially different from the standard-of-care dose (see Table 1 footnote e). Logistical feasibility refers to: (1) the timeliness of CURATE.AI dose recommendations to the physician; (2) participant adherence to CURATE.AI-recommended doses; (3) physician adherence to CURATE.AI recommended doses. We hypothesize that CURATE.AI will meet these feasibility criteria, as further defined in our outcome measures below, for the selected palliative-intent chemotherapy regimens and respective tumour markers. We will use these data to decide if and how a future RCT should proceed.

**Table 1 T1:** Outcome measures and progression criteria for the PRECISE CURATE.AI pilot clinical trial, based on “the traffic light system” recommended in the CONSORT extension statement for pilot clinical trials (33).

**Outcome measures**	**Green^*^**	**Yellow^*^**	**Red^*^**
**Primary Outcome Measures**			
Applicability of CURATE.AI profiles^a^	>70%	10–70%	<10%
**Secondary Outcome Measures**			
Patient adherence^b^	>90%	10–90%	<10%
Timeliness of CURATE.AI dose recommendations to the physician^c^	100%	10–99%	<10%
Physician adherence^d^	>70%	10–70%	<10%
Clinically significant dose changes^e^	>20%	1–20%	0%
**Exploratory Outcome Measures**			
Efficacy: (1) Clinical progressive disease^f^ (2) Temporal variation in tumour marker level (3) Maximal reduction in tumour marker level	N.A.	N.A.	N.A.
Clinically relevant toxicities^g^	N.A.	N.A.	N.A.
Data collection and exploratory analysis of CEA, CA19-9, and/or other traditional markers in higher frequency serial measurements after modulated dosing in relation to standard frequency readings and other efficacy measures (e.g., RECIST criteria).	N.A.	N.A.	N.A.
Data collection and exploratory analysis of ctDNA as: (1) a tumour marker in serial measurements at given clinical context and after modulated dosing (2) a potential input for CURATE.AI	N.A.	N.A.	N.A.

*See section on Data Collection, Management and Analysis.*

*
*Green: a future randomised trial is definitely feasible. Yellow: a future randomised trial is possibly feasible if its design is appropriately modified. Red: a future randomised trial is unfeasible in its current form.*

a
*percentage of participants in whom we successfully apply CURATE.AI profile. A decision on whether we “successfully apply” the CURATE.AI profile requires expert judgement and cannot be made based on a purely numerical process. The expert panel will consider the following factors with careful regard for the individual circumstances of each participant: (1) error/variance (biological/analytical) is allows accurate predictions (see section primary outcome measure); (2) profile can be generated sufficiently early for the participant to potentially benefit; (3) dose-dependent relationship is observed; (4) profile is actionable (i.e., fulfils the clinical investigator's pre-specified safety requirements); (5) systemic changes in the participant which require profile recalibration are rare or readily assimilated into the CURATE.AI algorithm.*

b
*percentage of participants who always adhered to the prescribed dose whenever they took their medication, as measured by the standardised pharmacovigilance protocol.*

c
*percentage of CURATE.AI recommendations provided in time for the next chemotherapy cycle, across all participants and cycles.*

d
*percentage of CURATE.AI recommended doses that were used by the clinical investigator.*

e
*percentage of participants in whom the CURATE.AI-guided cumulative dose is substantially (≥10%) different from the projected standard-of-care cumulative dose, which is defined as the maximum dose of capecitabine (1,000 mg/m^2^ twice daily for XELOX and XELIRI regimen, 1,250 mg/m^2^ twice daily for single agent capecitabine regimen) multiplied by the number of completed chemotherapy cycles.*

f
*defined as the clinical investigator deeming that the patient will not benefit any further from the chemotherapy regimen and considering stopping it, at the time of the first radiological assessment performed as per standard-of-care.*

g
*of grades 3–4 based on Common Terminology Criteria for Adverse Events (CTCAE) version 4.0.*

*ctDNA, circulating tumour DNA*.

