### Study Setting and Participant Recruitment

We will recruit participants at two centres: National University Hospital (NUH) and Ng Teng Fong General Hospital (NTFGH), which both belong to the National University Health System (NUHS), Singapore. Clinical investigators will recruit patients from outpatient clinics during routine clinical reviews, weekly trial meetings or multidisciplinary tumour boards. As this is a pilot clinical trial with no precedent data, we intend to first recruit 10 patients and perform an interim analysis, which will include formal power and statistical sample size calculations. Based on these outcomes, we will consider an RCT, or an amendment of this study protocol to expand the current cohort or to include further cohorts of patients with a wider range of chemotherapy regimens or tumour markers. We will consider participants to be evaluable for the primary outcome measures only if participants are able to complete the first two cycles of chemotherapy in an uninterrupted manner. We will replace any unevaluable participants with new participants, though we will continue to monitor and report any adverse events in the unevaluable participants. We will consider replacing participants who withdraw from the study (see Supplementary Text) with new participants if we could not collect sufficient data for primary outcome assessment.

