### Sample Size

Since this is a pilot clinical trial with no precedent data, we did not perform an upfront formal sample size calculation. We intend to first recruit 10 patients and perform an interim analysis using the data generated from these participants, which will include formal power and statistical sample size calculations. Based on these outcomes, we will consider cohort expansion or an RCT.

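### At 10 participants the primary Green band (8/10 or more) cannot support a conclusion that an RCT is definitely feasible; as a minor matter, the timeliness bands leave 99–100% unassigned

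*Protocol article*

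**What the plan says.** Table 1 of the protocol article sets traffic-light progression criteria. The primary row reads "Applicability of CURATE.AI profiles^a^ >70% 10–70% <10"%, that is, Green above 70%, Yellow from 10% to 70% and Red below 10%. The table footnote gives the meaning of the colours: "Green: a future randomised trial is definitely feasible. Yellow: a future randomised trial is possibly feasible if its design is appropriately modified". Red means that a trial is not feasible in its current form. The section on the primary outcome measure confirms that these bands are the progression criteria for the RCT.

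The Sample Size section fixes the first decision point: "We intend to first recruit 10 patients and perform an interim analysis using the data generated from these participants". It also states that "we did not perform an upfront formal sample size calculation". Under Study Setting and Participant Recruitment, "We will replace any unevaluable participants with new participants", so the intended denominator is 10 evaluable participants. After the interim analysis the options are an RCT or expansion of the cohort.

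Among the secondary outcomes, the row "Timeliness of CURATE.AI dose recommendations to the physician^c" has Green at 100%, Yellow at 10–99% and Red below 10%. Footnote c counts it over all recommendations, participants and cycles.

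**The concern.** The pilot exists to decide whether and how an RCT should go ahead, and the colour of the primary outcome is the main input to that decision. Green is worded as a statement of certainty, but it can be reached with 8 successes among 10 people. If the data at that point are also compatible with a success rate well inside Yellow, the pilot will have announced more than it has shown. An RCT could then be launched unmodified when the trial's own scale would have called for a change of design.

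The timeliness bands raise a smaller question of completeness: a prespecified rule should give a colour to every value that can be observed.

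**Working it through.** **Inputs.** n = 10 (Sample Size; unevaluable participants are replaced). Primary bands >70%, 10–70% and <10% (Table 1). Timeliness bands 100%, 10–99% and <10% (Table 1), counted over all recommendations. Cycles last 3 weeks (Choice of Chemotherapy Regimens), with at most 12 months per participant (Study Timeline and Investigations). The article states no expected success rate, alpha or power, so there is no planning figure to reproduce. The true rates p below are assumptions, shown as a range.

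**Step 1: bands as counts.** With x successes in 10, Red needs x/10 < 0.10, so x = 0. Green needs x/10 > 0.70, so x ≥ 8, because 7/10 is exactly 70% and therefore Yellow. Yellow is x = 1 to 7.

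**Step 2: precision of a Green result.** Exact (Clopper–Pearson) two-sided 95% intervals:

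| Result | 95% interval |
|---|---|
| 8/10 | 44.4–97.5% |
| 9/10 | 55.5–99.7% |
| 10/10 | 69.2–100% |

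For 10/10 the lower limit is 0.025^(1/10) = 0.692. No Green count excludes 70% on a two-sided 95% interval. On a one-sided 95% bound, 10/10 just does (0.05^(1/10) = 0.741), but 9/10 (60.6%) and 8/10 (49.3%) do not.

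**Step 3: chance of each colour.** P(Red) = (1 − p)^10. P(Green) = Σ C(10,k) p^k (1 − p)^(10−k) for k = 8, 9, 10.

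At p = 0.6: 45(0.6^8)(0.4^2) + 10(0.6^9)(0.4) + 0.6^10 = 0.1209 + 0.0403 + 0.0060 = 0.167.

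At p = 0.7: 45(0.7^8)(0.3^2) + 10(0.7^9)(0.3) + 0.7^10 = 0.2335 + 0.1211 + 0.0282 = 0.383.

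| True rate | P(Red) | P(Yellow) | P(Green) |
|---|---|---|---|
| 5% | 0.599 | 0.401 | <0.001 |
| 10% | 0.349 | 0.651 | <0.001 |
| 20% | 0.107 | 0.893 | <0.001 |
| 30% | 0.028 | 0.970 | 0.002 |
| 50% | 0.001 | 0.944 | 0.055 |
| 60% | <0.001 | 0.833 | 0.167 |
| 70% | <0.001 | 0.617 | 0.383 |
| 80% | <0.001 | 0.322 | 0.678 |

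**Step 4: timeliness gap.** With one late recommendation among N, the value is (N − 1)/N. It exceeds 99% only if N > 100: 99/100 = 99.0% is Yellow, while 100/101 = 99.01% has no band. At one recommendation per cycle, the ceiling is 10 × 365/21 = 173.8, about 174, where one late gives 173/174 = 99.4%. Two late would need N > 200, which is out of reach with 10 participants. Rounded to a whole percent, every reachable value in the gap becomes 99% and so Yellow; rounding up to 100% would need N ≥ 200.

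**The case against.** The strongest reply is that this is a pilot. It openly makes no formal sample size calculation, 10 participants are a first stage with expansion as a listed option, and the article says that the statistics will be viewed in a broader clinical context. All of that stands, and neither the sample size nor the absence of a power calculation is criticised here. None of it changes what the footnote says Green means, however. An RCT is one of the options at the 10-patient analysis, so the wording has to be defensible at that number.

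A reader might go further and infer that the rule almost never stops a poor platform, because Red requires zero successes. The documents do not support that. Red occurs 60% of the time at a true rate of 5% and 35% at 10%. It becomes rare (under 3%) only from about 30% upward. Weak platforms that escape Red fall in Yellow, which makes feasibility conditional on changing the design; at true rates of 10–30% the chance of Green is at most 0.2%. A low Red line also fits the aim of identifying which patients the method works in, since a few successes may mark a usable subset.

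Nor does it follow that Red should move, for example to 3/10 or fewer. That is a trade-off: at a true 40%, P(x ≤ 3) = 0.0060 + 0.0403 + 0.1209 + 0.2150 = 0.382, so such a platform would be stopped 38% of the time.

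Patient adherence invites a similar inference, since Green above 90% means 10/10. Relaxing it to 90% or more would make 9/10 both Green and Yellow (10–90%), a contradiction that the table does not now contain.

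**Conclusion.** The point holds for the wording of Green. With 10 participants, a Green primary result is compatible with true success rates inside Yellow: down to 44% at 8/10 and 69% at 10/10. A true 60% or 70% is labelled Green 17% or 38% of the time. The design can support a decision to go on to planning an RCT, but not a claim of certainty. The criticism does not extend to the position of the Red cut-off, the adherence band or the size of the pilot.

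The timeliness gap is literally present but minor. It needs more than 100 recommendations with exactly one late, and ordinary whole-percent reporting would hide it.

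These figures assume 10 evaluable participants whose outcomes are independent with a common underlying success rate, and about one recommendation per cycle. The true rates are illustrative, because the article gives none. If the cohort is expanded, the counts change with the denominator and the intervals narrow.

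**What to change.** In Table 1:

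- Replace the description of Green with wording such as *proceed to planning a randomised trial*. Leave the percentage cut-offs for the primary outcome as they are.
- Report each participant-level percentage (applicability, patient adherence, clinically significant dose changes) with its count and exact 95% interval, and state that the band is read together with that interval. Timeliness and physician adherence count several recommendations per participant, so a simple binomial interval is not proposed for them.
- Change timeliness Yellow to *10% to <100%*, so that every value has a colour.

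This needs no more participants and no new data. Recruitment began in August 2020, but no primary threshold moves, and the timeliness edit only gives a colour to values that had none. The downside is a less emphatic conclusion when the result is Green.

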#### Secondary and Exploratory Outcome Measures

The secondary outcome measures (Table 1) focus on both technical and logistical feasibility, which constitute our primary objectives. Secondary outcomes include: (1) patient adherence to the prescribed dose; (2) timeliness of CURATE.AI recommendations to the physician in time for the next chemotherapy cycle, across all participants and cycles; (3) physician adherence to CURATE.AI recommended doses; (4) clinically significant dose changes where a participant's CURATE.AI-guided cumulative dose is ≥10% different from the projected standard-of-care cumulative dose.

Exploratory outcome measures (Table 1) mainly relate to efficacy and toxicity, which constitute our secondary objectives. Exploratory outcomes relating to efficacy include: (1) percentage of trial participants with clinical progressive disease defined as the clinical investigator deeming that the patient will not benefit any further from the chemotherapy regimen and considering stopping it, at the time of the first radiological assessment performed as per standard-of-care; as well as (2) temporal variation and (3) maximal reduction in tumour marker level from trial initiation to conclusion. We will also measure clinically relevant toxicities of grades 3–4 as an exploratory outcome, using the Common Terminology Criteria for Adverse Events (CTCAE) version 4.0. Other exploratory outcomes include data collection and exploratory analysis of CEA, CA19-9 and/or other traditional tumour markers in higher frequency serial measurements after modulated dosing in relation to standard frequency readings and other efficacy measures, e.g., RECIST criteria. Finally, we will perform data collection and exploratory analysis of ctDNA as a tumour marker in serial measurements at given clinical context and after modulated dosing, as well as a potential input for CURATE.AI. However, we will not use the analysis of ctDNA to prospectively guide drug dosing in this pilot clinical trial.

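### Patient adherence is scored only on occasions when medication was taken, so omitted capecitabine doses cannot lower a measure that carries a progression threshold

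*Protocol article*

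**What the plan says.** Footnote b to Table 1 gives the operational definition: "percentage of participants who always adhered to the prescribed dose whenever they took their medication". It is scored per participant, all or nothing, and only on occasions when medication was taken. The pharmacovigilance protocol it names for measurement is not part of the article.

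Elsewhere the same concept has no such condition. The Primary Objective names "participant adherence to CURATE.AI-recommended doses" as one of three components of logistical feasibility, and the Abstract describes it in similar terms. The section on Secondary and Exploratory Outcome Measures lists "1) patient adherence to the prescribed dose".

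Table 1 sets Green above 90%, Yellow from 10% to 90% and Red below 10% for this measure. By the table's own key, Green on a measure means that a future randomised trial is definitely feasible. The Sample Size section plans 10 participants before the interim analysis.

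**The concern.** The condition removes the commonest meaning of non-adherence, not taking the drug, from a measure called adherence. A participant who skips many doses but takes the right amount each other time counts as fully adherent. A participant who takes one wrong amount in up to 12 months counts as non-adherent.

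Omission is foreseeable here. Capecitabine is given twice daily (Table 1, footnote e), it is the only drug that CURATE.AI modulates, and the section on Choice of Chemotherapy Regimens says that many patients tolerate its maximum tolerated dose poorly. At stake is a Green light on patient adherence, one of the inputs to the decision on a randomised trial, given without testing whether participants took the doses scheduled for them.

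**Working it through.** The plan states no adherence calculation, so there is no figure to reproduce. The check has three steps.

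**1. Apply footnote b to a participant with omissions.** Let N be the number of scheduled doses, and assume that 25% are missed and the rest are taken at the prescribed amount.
- Footnote b: correct doses ÷ doses taken = 0.75N ÷ 0.75N = 100%, so adherent.
- Scheduled-dose basis: doses taken ÷ doses scheduled = 0.75N ÷ N = 75%.

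The missed share cancels in the first ratio, so the result is the same for any other share below 100%.

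**2. Carry this to the threshold.** Inputs: n = 10 (Sample Size) and Green above 90% (Table 1). Since 9/10 = 90% is not above 90%, Green needs 10 of 10. Let q be the share of participants who would be non-adherent because of omissions but always take the right amount when they take anything. Take the other participants as fully adherent and participants as independent. The values of q are assumptions.

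| q | Footnote b as worded | Expected adherence if omissions count | P(Green) = (1 − q)^10 |
|---|---|---|---|
| 0.1 | 100%, Green | 90% | 0.349 |
| 0.2 | 100%, Green | 80% | 0.107 |
| 0.3 | 100%, Green | 70% | 0.028 |
| 0.5 | 100%, Green | 50% | 0.001 |

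The second column does not move with q: the measure carries no information on omissions.

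**3. The dose entered in the model, as a conditional point only.** The section on calibration-intent recommendations says "CURATE.AI requires a minimum of three unique data pairs (capecitabine dose and tumour marker" and that one pair is collected per cycle. It does not say whether the dose is the one recommended, prescribed or taken.
- If the taken dose is entered, omissions cause no input error.
- If the prescribed dose is entered, missing an assumed 10%, 20% or 25% of doses at a prescribed 100% level means that 90%, 80% or 75% was taken.

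As an illustration of the second case, assume a true curve (x − 80)²/100 + 5, prescribed levels of 100%, 75% and 50%, and omissions in the 100% cycle only. The quadratic through the three recorded points then has its minimum at 85.5%, 88.2% or 87.5% instead of 80%. The curve is invented to show the mechanism and says nothing about actual doses.

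**The case against.** The strongest reply is that the article is a condensed account. The pharmacovigilance protocol may record missed doses, and the condition may be a loose way of saying *throughout treatment*. The measure is also one of four secondary outcomes, reported descriptively, while applicability of the profiles is the main outcome for technical feasibility. Participants must complete two uninterrupted cycles to be evaluable for the primary outcome, which may exclude some gross early omission.

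Part of this stands. The point concerns a secondary measure, and missed doses may well be recorded. But footnote b is a stated rule, not an absent detail. Applied as written, it leaves recorded omissions out of the outcome. The evaluability rule does not reach later cycles or say how isolated missed doses are treated.

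A reader might go further, in four ways that the article does not support:
- **That the dose–response data are corrupted.** Footnote b defines an outcome and does not decide which dose enters the model.
- **That omissions breach the protocol's own 10% limit.** That limit, in footnote e, compares the cumulative guided dose with the projected standard-of-care cumulative dose. It is not a tolerance for taken against prescribed dose.
- **That the need for 10 of 10 shows the same flaw.** With a true rate of 95% per participant, Green is reached with probability 0.95^10 = 0.599. That suggests the threshold is hard to reach, whereas the fault here is that omissions cannot prevent Green.
- **That the choice between recommended and prescribed dose is a serious contradiction.** Footnote d measures separately whether investigators used the recommendations, so judging patients against the prescribed dose is reasonable. Only the wording of the Abstract and Primary Objective needs to follow.

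**Conclusion.** The concern holds for the definition of the outcome. As worded, footnote b is blind to omitted doses, is narrower than the three other descriptions of the same measure, and can show Green at any omission rate. Under one *always* rule, counting omissions could only leave the result unchanged or lower it, so the condition errs in the favourable direction. The probabilities rest on assumed shares of participants, independence and a denominator of 10. They show how much the definition can hide, not what will happen. An error in the CURATE.AI input remains a possibility only, to be settled by stating which dose is used. The point deserves correction but does not undermine the primary outcome.

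**What to change.** Choose one of two wordings for footnote b:
1. Delete the condition on having taken medication. Count scheduled doses that were not taken as non-adherence, leave out investigator-directed holds, and replace *always* with a tolerance that the sponsor chooses and states in advance.
2. Keep the present test but name it correctness of dose when taken, and report omitted doses as a separate feasibility measure.

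Use *prescribed dose* consistently in the Abstract, the Primary Objective, footnote b and the secondary-outcome text. State in the section on calibration-intent recommendations which dose enters each data pair. If it is now the prescribed dose, record the dose actually taken instead.

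The cost is a few sentences. Reported adherence may be lower, although a tolerance would also stop one trivial error from making a participant non-adherent. Both options depend on the pharmacovigilance record capturing missed doses and the reason for each, which the article does not confirm.
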